#### Assessment of Disease Activity

To measure disease activity in participants with CD, we will assess a modified HBI without including the item on the presence of an abdominal mass (Table 3). HBI scores of <5, 5 to 7, 8 to 16, and >16 correlate with symptomatic remission, mildly active symptoms, moderately active symptoms, and severely active symptoms, respectively. A decrease in the HBI score of 3 or 4 correlates well with a symptomatic response [35].

In addition to calculating clinical remission and response using the aforementioned measures, we will create an outcome of steroid-free remission or response based on whether the patient was on concurrent steroids at the time of assessment. In patients with UC and indeterminate colitis, disease activity will be assessed with the SCCAI (Table 4). An SCCAI score of <3 has been shown to correlate with symptomatic remission, whereas a decrease of 2 points has been shown to correlate with a symptomatic response [36].

**Table 3 table3:** Modified Harvey-Bradshaw Index.

Item	Scoring
General well-being	Well: 0, fair: 1, poor: 2, terrible: 3
Abdominal pain	None: 0, mild: 1, moderate: 2, severe: 3
Number of liquid stools per day	Each liquid stool: 1
Arthralgia	Yes: 1, no: 0
Uveitis	Yes: 1, no: 0
Erythema nodosum	Yes: 1, no: 0
Aphthous ulcers	Yes: 1, no: 0
Pyoderma gangrenosum	Yes: 1, no: 0
Anal fissure	Yes: 1, no: 0
New fistula	Yes: 1, no: 0
Abscess	Yes: 1, no: 0

**Table 4 table4:** Simple Clinical Colitis Activity Index.

Item	Scoring				
	0	1	2	3	4
Bowel frequency (day)	1 to 3	4 to 6	7 to 9	>9	N/A^a^
Bowel frequency (night)	None	1 to 3	4 to 6	N/A	N/A
Urgency of defecation	None	Hurry	Immediately	Incontinence	N/A
Blood in stool	None	Trace	Occasionally frank	Usually frank	N/A
General well-being	Very well	Slightly below par	Poor	Very poor	Terrible
Aphthous ulcers	None	Present	N/A	N/A	N/A
Uveitis	None	Present	N/A	N/A	N/A
Erythema nodosum	None	Present	N/A	N/A	N/A
Arthralgia	None	Present	N/A	N/A	N/A

^a^N/A: not applicable.

We will calculate steroid-free remission as described in the previous paragraph. To assess disease activity using the Tappt system, we will use the PRO-2 assessments for CD [31] and UC [32]. These measures of PROs have been validated in IBD and demonstrate an association between improvements in patient-reported symptoms and clinical remission and response [37,38]. For CD, the PRO-2 assessment comprises questions regarding the frequency of bowel movements in the prior week and the degree of abdominal pain (Table 5). PRO-2 scores of 8, 14, and 34 correlated with Crohn’s Disease Activity Index [39] scores of 150, 220, and 450, respectively. A Crohn’s Disease Activity Index score of <150 is consistent with clinical remission, whereas a score of >220 is consistent with moderate to severe disease. In lieu of calculating a total score, an average liquid stool frequency per day of >4 or an average abdominal pain score of 2 (moderate) or higher will trigger an alert.

For UC and indeterminate colitis, a PRO-2 assessment specific for UC will be used. It comprises questions related to stool frequency and rectal bleeding (Table 6). A score of ≥2 for stool frequency or rectal bleeding will trigger an alert.

**Table 5 table5:** Patient-reported outcome scale, 2-item version, for patients with Crohn disease.

Variable	Day								7-day average		Weighting factor		Total
	1	2	3	4	5	6	7						
Number of liquid or very soft stools	—^a^	—	—	—	—	—	—	—		× 2 = —		—	
Abdominal pain (0=none, 1=mild, 2=moderate, 3=severe)	—	—	—	—	—	—	—	—		× 5 = —		—	

^a^To be filled in by health care staff.

**Table 6 table6:** Patient-reported outcome scale, 2-item version, for patients with ulcerative colitis.

Stool frequency	Rectal bleeding	Score
Normal number of stools	No blood seen	0
1 to 2 stools more than normal	Streaks of blood with stool less than half the time	1
3 to 4 stools more than normal	Obvious blood with stool most of the time	2
≥5 stools more than normal	Blood alone passes	3

In addition, the results of quantitative C-reactive protein and fecal calprotectin tests, if available, will be extracted from the medical record at each time point. Research staff will use the value closest to the time of assessment within 30 days. C-reactive protein correlates well with endoscopic disease activity (*r*=0.56), and values <5 mg/dL have negative predictive values for endoscopic disease activity ranging from 29% to 61% [40-42]. Likewise, fecal calprotectin correlates well with endoscopic disease activity (*r*=0.53) but has better negative predictive values for endoscopic disease activity ranging from 71% to 97% using a value of <250 mcg/g [42,43]. Similarly, we will collect information on endoscopic disease activity, if available. For UC and IBD type undetermined, we will use the Mayo Endoscopic Score (MES; Table S1 in Multimedia Appendix 1). The MES assessment was modified to remove friability in the mild disease category. An MES of 0 to 1 is consistent with endoscopic remission [44].

For patients with CD, we will assess endoscopic disease activity with the Simple Endoscopic Score (Table S2 in Multimedia Appendix 1). A score of <3 is consistent with inactive disease, 3 to 6 mildly active, 7 to 15 moderately active, and ≥16 severely active [45,46]. We will also record new steroid use (oral or topical treatment) in the interval between assessments.

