### Study Schedule

All participants are required to complete electronic data entry forms at baseline and at 12, 26, and 52 weeks. Adherence, disease activity, QoL, PROs, IBD self-efficacy, and health care use will be measured at each time point during the 1-year study (Table 1). Demographic and clinical information will be collected at the baseline visit.

**Table 1 table1:** Schedule of events for the study.

Instrument	Category	Source	Baseline	Week 12	Week 26	Week 52
Demographics	Demographics	Patient	✓			
Clinical history	Clinical information	Provider or site	✓			
Medication adherence	Adherence	Patient		✓	✓	✓
MARS-5^a^	Adherence	Patient	✓	✓	✓	✓
Health care use	Health care use	Patient	✓	✓	✓	✓
Modified Harvey-Bradshaw Index	Disease activity: CD^b^	Patient	✓	✓	✓	✓
Simple Clinical Colitis Activity Index	Disease activity: UC^c^	Patient	✓	✓	✓	✓
C-reactive protein	Disease activity	Provider or site	✓	✓	✓	✓
Calprotectin	Disease activity	Provider or site	✓	✓	✓	✓
Simple endoscopic score: CD	Disease activity	Provider or site	✓	✓	✓	✓
Mayo Endoscopic Score	Disease activity	Provider or site	✓	✓	✓	✓
PROMIS^d^ Global Health Scale	Quality of life	Patient	✓	✓	✓	✓
PROMIS anxiety	Mental health	Patient	✓	✓	✓	✓
PROMIS depression	Mental health	Patient	✓	✓	✓	✓
PROMIS sleep disturbance	Mental health	Patient	✓	✓	✓	✓
PROMIS fatigue	Disease activity	Patient	✓	✓	✓	✓
PROMIS pain interference	Disease activity	Patient	✓	✓	✓	✓
PROMIS physical function	Frailty	Patient	✓	✓	✓	✓
IBD^e^ self-efficacy	Self-efficacy	Patient	✓	✓	✓	✓

^a^MARS-5: Medication Adherence Report Scale-5.

^b^CD: Crohn disease.

^c^UC: ulcerative colitis.

^d^PROMIS: Patient-Reported Outcome Measurement Information System.

^e^IBD: inflammatory bowel disease.

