### Study Population

Patients will be recruited for this study from 5 clinical centers at the University of Maryland School of Medicine, University of Cincinnati School of Medicine, NYU Grossman School of Medicine, University of North Carolina School of Medicine, and Vanderbilt University School of Medicine.

Inclusion criteria will include (1) aged ≥18 years; (2) documented IBD based on usual diagnostic criteria, including clinical symptoms and findings from endoscopy, radiology studies, and histology [30]; (3) initiation of treatment with a new oral or subcutaneous treatment for IBD; (4) access to a smartphone with a reliable data plan or Wi-Fi access; and (5) ability to understand the protocol and provide informed consent in English. Exclusion criteria will include (1) inability to speak and read English or comply with the study protocol; (2) the presence of an ileostomy, colostomy, ileoanal pouch anastomosis, or ileorectal anastomosis; (3) initiation of oral corticosteroids only without concurrent use of an oral or subcutaneous maintenance therapy; (4) imminent surgery within the next 60 days; (5) history of short bowel syndrome; or (6) uncontrolled medical or psychiatric disease.

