### Study Conduct

Eligible patients will be approached by research staff at the time of routine clinical visits or via telephone and provide informed consent. All of the participants’ concomitant medications will be continued during the study. Corticosteroids will be tapered at the discretion of the investigator. Addition of new IBD medications will be allowed during the study. If the new medication is an eligible oral or subcutaneous addition to existing therapy, this will be tracked using the approach that was used to track the original medication during the initial treatment. If the new medication replaces the initial therapy, the replacement medication will be similarly tracked.

Participants will be randomized 2:1 to receive either remote monitoring or standard of care using a random permuted block design with randomly varied block sizes. Participants will be stratified based on study site and disease subtype (CD vs UC or indeterminate colitis). We chose to stratify on these variables because they could affect the response to the intervention; stratification will ensure balance of these covariates among the study groups. The randomization order will be computer generated, and group assignment will be made when a new participant is enrolled into the study by the clinical site. The site investigators and research staff will remain blinded to the randomization order. The participants and physicians will not be blinded to the group assignment; however, we will attempt to minimize measurement bias by collecting outcome data through electronic data capture directly from participants.

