At the time of taking a medication dose, participants will scan the label with their mobile phone to verify that they are taking the medication. Upon scanning, participants will immediately receive a notification on their device indicating that the label was successfully scanned and that their medication adherence was updated in their profile. Each day that a medication is due to be taken, participants will receive a reminder through SMS text message notifying them of their medication schedule for the day. If participants fail to scan the label at a given time (as determined by their specific medication regimen), they will receive an SMS text message at the end of the day with a link to respond to a survey that captures reasons for nonadherence.

Participants will also complete a PRO-2 assessment at baseline and then monthly for the entire 12 months of the study triggered by the Tappt system through an HTML link sent to patients by SMS text message [31,32]. For participants with CD, the PRO-2 assessment includes abdominal pain and liquid stool frequency. For participants with UC or indeterminate colitis, the PRO-2 assessment includes rectal bleeding and stool frequency. The research team will also be able to send the PRO-2 survey to patients at any given time, at their discretion, if patients are experiencing a flare or at the time of a change in medication dose. Items for the PRO-2 assessment vary based on disease type (refer to the Outcomes and Outcome Measures section).

Clinical teams can review their participants’ data in real time through the secure cloud-based provider-facing Tappt portal. To reduce monitoring burden among clinical teams, the system’s algorithms prompt automated email alerts to the clinical team when participants’ adherence or PROs fall below predetermined thresholds, when a participant’s regimen is approaching refill date, or when a participant reports an error on their profile. These alerts can support clinical teams in following up with patients in a timely manner to reduce risk for poor outcomes (Figure 1).

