### Outcomes and Outcome Measures

#### Overview

The outcome measures outlined in the following sections will be assessed at baseline and at 12, 26, and 52 weeks after initiating treatment. All outcome measures will be captured electronically and will not require a study or office visit.

The primary outcome of the proposed study will be the difference in mean MPR between the intervention and control groups during the 12-month study. The mean MPR will be calculated as follows:

MPR = number of days’ supply of medication obtained during observation period / total number of days in observation period.

If a participant discontinues therapy but initiates treatment with another eligible medication, the MPR will continue to be calculated. Any delay in initiating new treatment will be adjusted for the total number of days in the observation period (ie, if drug A is discontinued and drug B is started 2 weeks later, the observation period will be 365 – 14 = 351 days); for example, if a participant is prescribed oral mesalamine (1.2 g), 4 tablets daily, for 90 days (dispense 360) with 2 refills between months 6 and 12, the MPR would be 100%. Likewise, if a participant is prescribed ustekinumab 90 mg subcutaneous every 8 weeks (dispense 1 syringe) with 2 refills between months 6 and 12, the MPR would be 66%. Data on medication use will be self-reported by participants at each time point. However, we will randomly validate participant report via chart review of pharmacy data for 20% of the participants. Participants will report the date the medications of interest were filled as well as the number of days’ supply of medications filled. Self-reported adherence will be assessed with the Medication Adherence Report Scale-5 questionnaire (Table 2). Scores for each item are summed to give a total score, with higher scores indicating higher levels of reported adherence [33].

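### The 30-day rule for CRP and calprotectin has no direction at baseline, so a value drawn after randomization and the start of the new therapy can be recorded as baseline

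*Protocol article*

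**What the plan says.** All places are in the Methods of the protocol article.

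- **Assessment of Disease Activity.** CRP and calprotectin results, "if available, will be extracted from the medical record at each time point". The selection rule follows: "Research staff will use the value closest to the time of assessment within 30 days". Endoscopic findings are then described as collected in a similar way when they exist.
- **Study Schedule, Table 1.** Both markers and both endoscopic scores are ticked at baseline and at weeks 12, 26 and 52, with the provider or site as source.
- **Study Population.** Entry requires "initiation of treatment with a new oral or subcutaneous treatment for IBD".
- **Outcomes and Outcome Measures, Overview.** The outcome measures "will be assessed at baseline and at 12, 26, and 52 weeks after initiating treatment".
- **Study Conduct.** The "group assignment will be made when a new participant is enrolled into the study by the clinical site".
- **Intervention Group.** Intervention participants activate their account on enrollment, and the smart labels are shipped together with the first medication.
- **Statistical Analyses.** Demographic and clinical variables are compared between the groups at baseline. Variables that differ become candidates for adjustment in the regression models. Participants with and without data are also compared on baseline characteristics.

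No separate baseline rule and no before-or-after limit appears anywhere in the article.

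**The concern.** A rule that picks the nearest result on either side suits a follow-up visit, where a draw a little before or after the target day measures much the same state. Baseline is different. It is the point at which a new drug is started and an arm is assigned, so results on the two sides of it measure different things. A result from before describes the patient who entered the trial. A result from two or four weeks after may already reflect the new therapy and, in principle, the allocation.

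The rule also does more than fill gaps. When a true pre-treatment result exists but a later one lies nearer in time, the rule discards the true one.

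A baseline variable that allocation can touch loses the property that makes it safe to tabulate by arm, to screen as a confounder and to adjust for. Adjusting for it would be conditioning on something measured after randomization.

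**Working it through.** The plan gives no figure on this point, so there is none to reproduce, and the sample size is not involved. The check is window arithmetic, followed by asking what can be said about size.

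**1. Windows implied by the rule** (visit day ± 30, with baseline as day 0):

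| Visit | Day | Eligible days |
|---|---|---|
| Baseline | 0 | −30 to +30 |
| Week 12 | 84 | 54 to 114 |
| Week 26 | 182 | 152 to 212 |
| Week 52 | 364 | 334 to 394 |

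The baseline window ends on day 30 and the week 12 window opens on day 54, so one result cannot serve both visits. Of the 61 eligible baseline days, 30 fall after day 0: 30/61 = 49%. This is a share of calendar days, not of results.

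**2. Displacement.** Take a participant with calprotectin results on day −20 and day +15. The distances are 20 and 15 days, so the rule selects day +15 and drops the pre-treatment result.

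**3. Two separate clocks.** Assignment happens at enrollment, and the labels travel with the first medication. The first dose can therefore come after randomization, and the order of baseline survey, randomization and first dose is not fixed. A result drawn between randomization and first dose is free of drug effect but is still post-randomization. A clean baseline must precede both events.

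**4. Where the value is used.** Table 1 classes both markers as disease activity. The Statistical Analyses section does not list the clinical variables it will compare at baseline. Including these two is the natural reading, but it is not stated.

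**5. Size.** A calculation needs the share of participants with an early on-treatment test and the effect already present in that result. The documents give neither. By assumption only: let a share *q* of baseline values be drawn after the start, each carrying a fraction *f* of the later between-group effect Δ. The baseline difference is then *q·f*·Δ, and a change-from-baseline contrast keeps 1 − *q·f* of the effect:

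- *q* = 0.10, *f* = 0.25: 1 − 0.025 = 97.5%
- *q* = 0.25, *f* = 0.5: 1 − 0.125 = 87.5%
- *q* = 0.50, *f* = 1: 1 − 0.50 = 50%

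The range runs from trivial to severe, and nothing in the documents places the trial within it. It also takes the same *q* in both arms. If early testing were more frequent in one arm, the drug effect common to both arms would not cancel at baseline either.

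**6. Hidden change within one participant, also by assumption.** If a marker falls linearly to week 12, a day +30 value misses 30/84 = 36% of the fall and a day +15 value misses 15/84 = 18%. If it falls exponentially with an assumed 14-day half-time, the shares are (1 − 2^(−30/14)) / (1 − 2^(−84/14)) = 0.774/0.984 = 79% at day 30 and 0.524/0.984 = 53% at day 15.

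**The case against.** **The text never says the window is two-sided.** Correct. It states a distance and no direction. A reader could also argue that if extraction takes place at the baseline visit, a day +15 result does not yet exist. But the article does not say when extraction is done, and seeking the closest value naturally covers both sides. If only earlier results were meant, the sentence has to say so.

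**Window detail belongs in a full protocol or extraction manual.** This would answer a complaint that a rule is missing. Here an operative rule for site staff is stated, applies to every time point, and gives a wrong baseline value when followed as written.

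**These markers carry no main result.** This stands. They are chart data used when available. The primary outcome is MPR, compared by *t* test, and the secondary is health care use, compared by Wilcoxon test. Neither uses CRP or calprotectin. Response is defined on the symptom indices, and for the markers the article gives only absolute cut-offs.

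**Both arms start a new therapy, so early drug effect is shared.** This largely stands. The percentages in step 6 describe that shared effect in one participant, not bias between arms. It cancels between arms only if early tests are equally frequent and similarly timed in both. The article reports more noninvasive tests in the telemedicine arms of an earlier trial, which is indirect evidence and says nothing about the first 30 days here.

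**A reader might infer that a symptom alert from the baseline PRO-2 prompts an early laboratory test in the intervention arm.** The documents do not support this. The Intervention Group section says a symptom alert leads to contact by a clinical nurse and mentions no test order.

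**Conclusion.** The point holds as a defect in the baseline extraction rule for supportive measures. Followed as written, the rule allows a post-randomization, on-treatment CRP or calprotectin value to be recorded as baseline, even in place of an available pre-treatment one. It should be corrected, but it does not threaten the primary or the health care use comparison.

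A reader might go further and conclude that the trial's estimate of biomarker change to week 12 is understated by 36% or 79%. The documents do not support that. No change-from-baseline analysis of these markers is described, both figures sit at the extreme edge of the window, and the second rests on a single assumed half-time.

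The conclusion rests on two readings: that an undirected 30-day limit covers both sides of the assessment, and that the markers are among the clinical variables examined at baseline.

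**What to change.** In Assessment of Disease Activity, add a baseline-only rule: *baseline CRP and calprotectin are the latest results within the 30 days on or before both randomization and the first dose of the new therapy; if there is none, the baseline value is missing.* Both conditions are needed. A limit at first dose alone would still admit values drawn after randomization.

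Record the draw date with every extracted value, so that timing can be checked and the rule re-applied at analysis. Put the same on-or-before limit on baseline endoscopic scores. Keep the closest-within-30-days rule for weeks 12, 26 and 52.

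The cost is a sentence or two in the extraction rule and one date field, with no effect on sample size. On the calendar, 30 of 61 eligible baseline days are removed, so some participants will have no baseline biomarker value. How many cannot be told from the documents.

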#### Assessment of QoL and PRO Measures

The Patient-Reported Outcome Measurement Information System is a National Institutes of Health–funded instrument that assesses patients’ self-reported health over a 7-day period [47]. Patients report global health as well as different components of physical, mental, and social health, including physical function, anxiety, depression, fatigue, sleep disturbance, and pain interference; higher scores indicate poorer health (Tables S3-S9 in Multimedia Appendix 1). Patient-Reported Outcome Measurement Information System scores are standardized to the general population where a T-score of 50 is the standardized normal, with an SD of 10. Therefore, these measures can be considered within normal limits (<55), mild (55 to <60), moderate (60 to <70), and severe (≥70) based on domain scores measured in the general population in the United States. Minimally important differences of 2 to 6 points have been reported for other disease states, including chronic pain, stroke, osteoarthritis, and cancer [48].

